#### 4. STUDY DESIGN

This is a multicentre, single-arm, phase 2 study according to Simon's two-stage optimal design. This design has been applied to minimize the number of patients exposed to a possibly inactive drug, considering that alternative treatment options exist, although not satisfactory and likely to be more toxic. Patients who will receive at least one dose of study drug will be considered evaluable.

The primary endpoint will be the rate of evaluable patients alive and not progressed at 6 months.

The sample size calculation is based on the following statistical parameters:

- minimum acceptable rate of patients alive without progression at 6 months ( $p_0$ ) = 30%;
- auspicated rate ( $p_1$ ) = 50%
- type I and II errors = 10%.

According to these parameters, 22 evaluable patients should be enrolled at the first stage and the study will proceed to the second stage if at least 8 patients will be alive without progression after 6 months. At the second stage, further 24 evaluable patients will be enrolled for an overall sample of 46 evaluable patients. The study will be considered positive if at least 18 patients out of 46 will be alive without progression at 6 months. It is planned that 5 to 10 centres will participate in the study, which could be completed in 24 months.

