### 9.2. Secondary endpoints

- Toxicity: for each patient and for each type of toxicity, the worst degree suffered during treatment will be described.
- Objective response rate: defined as the number of complete plus partial responses divided by the number of patients enrolled.
- Progression free-survival: defined as the time from registration to progression or death without progression, whichever occurred first. Patients without progression at the end of the study will be censored at the date of the last visit when eventual progression was verified.
- Overall survival: defined as the time from registration to the date of death due to any cause. Patients still alive at the end of the study will be censored on the date of the last information on vital status.
- Metabolic response: defined as a reduction  $\geq 50\%$  of SUVmax after 2 weeks of treatment.

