## 10.2. Statistical analysis of biomarkers

Due to the small sample size, statistical analysis of biomarkers data will be conducted with the aim of hypothesis generation.

First of all, a complete description of data from biological and pharmacogenomic studies will be done. For biomarkers that might change over time as a consequence of treatment, levels before and after treatment will be compared with appropriate statistical tests, based on the type of data.

Outcomes of treatment will be compared between different VEGF and VEGFR phenotypes, with appropriate statistical tests.

P values  $\leq 0.05$  will be considered significant, and no adjustment is planned for multiple comparisons due to the exploratory nature of the analysis.

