## 11. TUMOR METABOLIC EVALUATION

Our group has shown that early FDG-PET-CT is able to predict survival outcomes in colorectal rectal cancer (32). Therefore PET-CT scans are planned at:

- baseline (within 2 weeks before treatment start)
- 14 (+/- 2) days after treatment start.

Patients will be fasted for at least 6 hours and blood glucose level will have to be less than 150 mg/dL for the study to be eligible for further quantitative analysis.

PET images will be reconstructed using iterative reconstruction and normalized for injected dose and patient body weight. Image analysis will be performed utilizing a semi-automatic region-of-interest (ROI) drawing software package where a three-dimensional region will be drawn around the area of increased uptake. Threshold values will be adjusted in order to encompass the area of increased uptake visually.

For each tumor volume, the following parameters will be calculated:

- $SUV = (\text{measured activity concentration [Bq/mL]} / (\text{injected activity [Bq]} / \text{body weight [kg]} \cdot 1,000))$ .
  - o SUV-max = the maximum pixel value measured in the visualized lesion
  - o SUV-mean = the average activity values in the ROIs.
- TLG (Total Lesion Glycolysis) =  $SUV\text{-mean} \times \text{metabolic tumor volume (mm}^3\text{)}$

On the basis of these parameters, the following indicator will be calculated for each patients, in order to assess metabolic response:

- Highest SUVmax = the highest SUVmax value among all the evaluable lesions
- Total SUVmax = the sum of the SUVmax value of all the evaluable lesions
- Highest TLG = the highest TLG value among all the evaluable lesions
- Total TLG = the sum of the TLG value of all the evaluable lesions

PET response will be calculated by measuring changes reported at the post treatment examination (14 +/- 2 days after treatment start) compared to the baseline test. For all the indicators the change will be calculated as:

$$\Delta = (\text{value-post} - \text{value-baseline}) / \text{value-baseline} \times 100$$

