Consistent with previous studies (32-34) the threshold to define a patient as responder according to change of SUV or TLG indicators is  $\leq -50\%$ . Therefore, patients with any change above these thresholds will be defined as non-responder. This value will be validated within this study for its predictive ability of survival outcome. Further thresholds will be eventually explored only in case of failure (lack of predictive ability) of the proposed validation.

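### The −50% PET threshold has neither one responder definition nor one deciding test: section 9.2 uses SUVmax alone, while section 11 uses four SUV and TLG indicators and an unnamed survival outcome

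*Protocol*

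**What the plan says.** Protocol section 9.2 lists metabolic response among the secondary endpoints: "Metabolic response: defined as a reduction" in SUVmax of 50% or more, two weeks into treatment. It does not say whether SUVmax is that of the hottest lesion or the sum over lesions, and it does not mention TLG.

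Protocol section 11 introduces a list with the words "the following indicator will be calculated for each patients, in order to assess metabolic response". The list has four entries: highest SUVmax, total SUVmax, highest TLG and total TLG. A patient is a responder when the change in the SUV or TLG indicators is −50% or lower, a value taken from earlier studies. The section goes on: "This value will be validated within this study for its predictive ability of survival outcome". After that comes: "Further thresholds will be eventually explored only in case of failure (lack of predictive ability) of the proposed validation".

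Section 9.2 contains two survival endpoints, PFS and OS. Section 2.2 places early PET assessment among the items to be explored. Section 10.2, on biomarkers, describes its purpose as generating hypotheses, sets significance at 0.05 and states that "no adjustment is planned for multiple comparisons due to the exploratory nature of the analysis".

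**The concern.** Two things are fixed badly in the text itself. First, the same secondary endpoint is defined in two ways. Section 9.2 leaves TLG out and section 11 brings it in, and even within SUVmax the choice between highest and total is open. The reported metabolic response rate would depend on which reading the analyst adopts.

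Second, section 11 promises to validate a threshold without naming one indicator and one outcome that would decide the matter. That choice could be made after the results are known. A reader of the final report could then take as validated a threshold that had merely reached significance on one of several possible pairs, in a small trial whose PET aim is exploratory.

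**Working it through.** **Step 1. Patients available.** The only sample size in the protocol is for the primary endpoint. Section 4 gives "minimum acceptable rate of patients alive without progression at 6 months" as 30%, "auspicated rate" as 50%, and both error rates as 10%. The rule is 22 patients, continue with at least 8 successes, 46 in total, positive with at least 18. With b the binomial probability and X₂ the successes among the 24 second-stage patients:

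P(positive | p) = Σ (x = 8 to 22) b(x; 22, p) · P(X₂ ≥ 18 − x; 24, p)

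This gives 0.0974 at p = 0.30 and 0.905 at p = 0.50. A full search for the optimal Simon design returns the same rule, so the stated figure reproduces. It provides at most 46 patients for PET, or 22 if the trial stops after the first stage of section 4. The protocol gives no power or success criterion for the PET question.

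**Step 2. Is responder status unique?** Take three lesions with SUVmax 10, 4 and 4 at baseline and 4, 4 and 4 on day 14 (an illustration).
- Highest SUVmax: (4 − 10)/10 = −60%, a responder.
- Total SUVmax: (12 − 18)/18 = −33%, a non-responder.

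Both readings satisfy section 9.2. TLG adds another route to disagreement, because section 11 computes it as SUV-mean times metabolic volume. A loss of volume can take TLG past −50% when SUVmax has fallen by less.

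**Step 3. How many tests could serve as the validation?** Four indicators with one outcome give 4; with PFS and OS they give 4 × 2 = 8.

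**Step 4. Chance of a false validation.** Assume that any one significant pair would be accepted at an unadjusted 0.05. Section 11 states neither the level nor the rule. For k independent exact tests the chance under no association is 1 − 0.95^k:
- k = 4: 1 − 0.95⁴ = 18.5%
- k = 8: 1 − 0.95⁸ = 33.7%

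The tests are correlated, since highest and total values share lesions. Two simulations under no association allow for this. One uses equally correlated normal statistics. The other uses log-rank tests with 30% responders, correlation 0.8 to 0.6 between the indicators before they are cut, correlation 0.6 between the log times of the two outcomes, no censoring and 1,500 trials per setting.

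| Setting | 1 test | 4 tests | 8 tests |
|---|---|---|---|
| Independent, exact | 5.0% | 18.5% | 33.7% |
| Equal correlation 0.5 | 5% | 15.5% | 25.0% |
| Equal correlation 0.7 | 5% | 13.0% | 19.0% |
| Equal correlation 0.9 | 5% | 9.4% | 11.8% |
| Log-rank, n = 46 | 6.2–6.5% | 15.3–18.4% | 27.8–30.9% |
| Log-rank, n = 22 | 6.5–8.1% | 18.9–24.6% | 29.9–39.4% |

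The log-rank figures at n = 22 partly reflect small-sample error of the test itself, as the single-test column shows.

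**Step 5. The opposite error.** By Schoenfeld's formula, power = Φ(√(D·a·(1 − a))·|ln HR| − 1.96), where D is the number of events and a the responder share. For an assumed HR of 0.5 with 46 events:
- a = 0.10: 29%
- a = 0.20: 47%
- a = 0.30: √(46 × 0.21) = 3.108; 3.108 × 0.693 − 1.96 = 0.19; power 58%
- a = 0.50: 65%

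With 22 events the range over the same shares is 16–37%. Even one named test is weak evidence here, which is a further reason not to speak of validation.

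**The case against.** The strongest reply is that little depends on this. PET is an exploratory aim in section 2.2, section 9 calls all analyses descriptive, and the notes to Table 6 withhold the day-14 PET results from the treating physician and the patient. No trial decision uses them. The 0.05 level belongs to the biomarker section, and section 11 nowhere says that success on any pair will do. The choice of outcome and test may sit in a statistical analysis plan that is not at hand. Section 11 can also be read as adding descriptive indicators to the section 9.2 endpoint.

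Much of this stands and limits the point. Three stronger readings that a reader might infer are not supported:

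- **That the validation can hardly fail.** The −50% value is fixed in advance from earlier studies. On the figures above, a worthless threshold would still fail in roughly two thirds to nine tenths of trials, and a real effect would often be missed.
- **That this is a confirmatory objective.** The aims say the opposite. The fault is one verb that does not fit them.
- **That the later search for thresholds inflates the validation.** It starts only after −50% has failed, and the protocol calls it exploration. In the log-rank simulation with seven cut-points, some significant threshold turned up in 73–80% of null trials at n = 46. That describes finding a new threshold, not validating −50%. It shows only why a new threshold would need independent data.

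What the reply does not remove is the text itself. An analysis plan could choose an indicator, but sections 9.2 and 11 would still differ, and section 11 would still promise a validation.

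**Conclusion.** The point holds as a conflict of definition together with a validation claim that has no single deciding test. The mismatch needs no assumption: SUVmax alone, highest or total unstated, against four SUV and TLG indicators.

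The size is conditional. If any of four to eight pairs were accepted at an unadjusted 0.05, the chance of a false validation would be about 9–34%. For eight tests it would be 12–25% at correlation 0.9–0.5, or about 28–31% in the log-rank simulation at n = 46. One named test gives about 5–8%. These figures rest on the assumed level, acceptance rule, correlations and responder share, and on every patient having an evaluable PET pair and an event. The primary endpoint and its design are not affected. The change is worth making because it removes a choice that could otherwise be made after seeing the data.

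**What to change.** Write the same single indicator into sections 9.2 and 11, for example highest SUVmax with a change of −50% or lower. In section 11 name one survival outcome, for example PFS, for the one test of that threshold, and state what result counts as failure. Label the other three indicators, the other outcome and any new threshold as exploratory and in need of independent data. Replace the promise to validate with wording suited to an exploratory aim, such as assessing the association in this trial. Counting PFS from the day-14 scan among patients still progression-free is an optional refinement.

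The cost is wording in two sections, with no extra scan or patient. The drawback is that only one indicator can support the claim.

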## 12. QUALITY ASSURANCE AND MONITORING

The procedures set out in this study protocol are designed to ensure that the principles of the Good Clinical Practice guidelines of the International Conference on Harmonization (ICH) and the Declaration of Helsinki are respected in the conduct, evaluation and documentation of this study.

Centralized monitoring activities are planned for 100% of the data. Peripheral monitoring of source data will be performed at discretion of the coordinating centre. , with peripheral auditing visits planned in case of need.

## 13. DATA COLLECTION PROCEDURES

Patient registration and data collection are centralized at the Clinical Trials Unit of the National Cancer Institute of Naples.

Patient registration is web-based (<http://www.usc-intnapoli.net>) or by telephone. Data collection is electronic at the above website.

## 14. PERSONAL DATA PROTECTION PROCEDURES

In order to protect the *privacy* of patients enrolled in the study, the following procedures will be used:

- the Coordinating Center, which has centralized responsibility for registration, randomization and data collection and processing procedures, will not allow access to the data, except to public authorities responsible for inspections under the relevant legislation (Health Ministry, Ethics Committee);
- at registration, patients will be assigned a numerical identification code (corresponding to progressive numbers of patients enrolled in the study) that will be noted together with the participating center's code for all the CRFs (web or paper based) and that will be used in all communications regarding individual patients;
- a list of patient codes and names will be kept by the Participating Investigator Center;
- documents that are not for submission to the Coordinating Center (eg, signed informed consent forms) should be kept in strict confidence by the investigator.

## 15. ETHICAL CONSIDERATIONS

### 15.1. Risk of undertreatment

The Simon's optimal two-stage study design has been chosen in order to minimize the number of patients exposed to a potentially inactive treatment, considering that alternative treatment options exist, although not satisfactory and likely to be more toxic. Moreover, an intensive schedule of response evaluation has been planned (6 and 12 weeks after treatment start) that allows to detect cases of early progression, with the aim of offering patients alternative treatment options.

### 15.2. Risk of toxicity (overtreatment)

In principle, there is no risk of overtreatment as this study is evaluating the activity of a biologic drug monotherapy in a population that alternatively may receive in clinical practice a combination chemotherapy that is expected to be more toxic. Moreover, an intensive clinical and laboratory assessment is scheduled for the first two cycles of treatment, to closely monitor the occurrence of regorafenib-related adverse events (that are generally early and temporary).

## 16. SUBJECTS INFORMATION AND CONSENT

All relevant information on the study will be summarized in an integrated subject information sheet and ICF provided by the Sponsor or the study center. A sample subject information and ICF is provided as a document separate to this protocol.

Based on this subject information sheet, the investigator or designee will explain all relevant aspects of the study to each subject/legal representative or proxy consentor (if the subject is under legal protection), prior to his/her entry into the study (ie, before any examinations and procedures associated with the selection for the study are performed or any study-specific data are recorded on study-specific forms).

The investigator will also mention that written approval of the IEC/IRB has been obtained.

Each subject/legal representative or proxy consentor will have ample time and opportunity to ask questions and will be informed about the right to withdraw from the study at any time without any disadvantage and without having to provide reasons for this decision.

Only if the subject/legal representative or proxy consentor voluntarily agrees to sign the ICF and has done so, may the subject enter the study. Additionally, the investigator and other information provider (if any) will personally sign and date the form. The subject/legal representative or proxy consentor will receive a copy of the signed and dated form.

The signed ICF is to remain in the investigator site file or, if locally required, in the subject's note/file of the medical institution.

The ICF and any other written information provided to subjects/legal representatives or proxy consentors will be revised whenever important new information becomes available that may be relevant to the subject's consent, or there is an amendment to the protocol that necessitates a change to the content of the subject information and/or the written ICF. The investigator will inform the subject/legal representative or proxy consentor of changes in a timely manner and will ask the subject to confirm his/her participation in the study by signing the revised ICF. Any revised written informed consent form and written information must receive the IEC's/IRB's approval/favorable opinion in advance of use.

## 17. ADMINISTRATIVE ASPECTS

- The study is a non-profit investigator initiated trial.
- The National Cancer Institute of Napoli is the non-profit sponsor of the study and will be responsible for protocol development, regulatory approvals, data collection, drug distribution and pharmacovigilance, monitoring, data analysis and publication.
- Regorafenib will be provided for free by the manufacturer.
- The study is planned to be multicentre in Italy and 5 to 10 centres are expected to participate.
- The sponsor will provide an insurance policy to cover possible damages caused to patients participating in the trial. The policy will cover all participating centers.
- Study protocol, patient information and informed consent will be submitted to Independent Ethical Committees and will only be started after their approval. Independent Ethical Committees will be periodically informed of study progress, safety and planned or premature end of the study.

## 19. APPENDICES

### 19.1. Eastern Cooperative Oncology Group performance status

| Grade | Description                                                                                                                                             |
|-------|---------------------------------------------------------------------------------------------------------------------------------------------------------|
| 0     | Fully active, able to carry on all pre-disease performance without restriction                                                                          |
| 1     | Restricted in physically strenuous activity but ambulatory and able to carry out work of a light or sedentary nature (eg, light housework, office work) |
| 2     | Ambulatory and capable of all self-care but unable to carry out any work activities. Up and about more than 50% of waking hours.                        |
| 3     | Capable of only limited self-care, confined to bed or chair more than 50% of waking hours                                                               |
| 4     | Completely disabled. Cannot carry on any self-care. Totally confined to bed or chair.                                                                   |
| 5     | Death                                                                                                                                                   |

## 19.2. Glomerular filtration rate

In accordance with established nephrology practice and guidelines, renal function at baseline and throughout the study will be assessed by means of the estimated GFR, calculated using the abbreviated MDRD study formula.

This equation of four variables (serum creatinine level, age, sex, and ethnicity) is recommended by the National Kidney Foundation for use in individuals 18 years or older. The formula is as follows:

aMDRD formula

$$\text{GFR (mL / min / 1.73m}^2\text{)} = k \times 186 \times [\text{serum creatinine}]^{-1.154} \times [\text{age}]^{-0.203}$$

Where  $k = 1$  (men) or  $0.742$  (women), GFR indicates glomerular filtration rate, and serum creatinine is measured in mg/dL.

Correction factor for eGFR calculation is  $0.881$  for Japanese subjects,  $1.227$  for Chinese subjects, and  $1.110$  for Korean subjects.a

Subjects with a baseline GFR  $< 30$  mL/min calculated by this method will not be allowed to participate in the study.

a. Matsuo S, Yasuda Y, Imai E, Horio, M (2010): Current status of estimated glomerular filtration rate (eGFR) equations for Asians and an approach to create a common eGFR equation. *Nephrology* 15, 45-48.

### 19.3. CYP3A4 inhibitors/inducers

The strong inhibitors and inducers of CYP3A4 listed here should be avoided during this study:

| CYP 3A4 Inhibitors            | CYP 3A4 Inducers                 |
|-------------------------------|----------------------------------|
| Amiodarone                    | Ajmaline d            |
| Aprepitant a       | Avasimibe d           |
| Boceprevir c       | Barbiturates                     |
| Chloramphenicol               | Carbamazepine d       |
| Cimetidine b       | Enzalutamide d        |
| Ciprofloxacin                 | Efavirenz                        |
| Clarithromycin c   | Fosphenytoin d        |
| Cobicistat c       | Glucocorticoids                  |
| Delavirdine c      | Methylphenobarbital d |
| Diethyl-Dithiocarbamate       | Mitotane d            |
| Diltiazem a        | Modafinil                        |
| Erythromycin a     | Nevirapine                       |
| Fluconazole a      | Oxcarbazepine                    |
| Fluvoxamine                   | Phenobarbital d       |
| Gestodene                     | Phenytoin d           |
| Grapefruit Juice c | Pioglitazone                     |
| Imatinib                      | Primidone d           |
| Indinavir c        | Rifabutin                        |
| Itraconazole c     | Rifampicin d          |
| Ketoconazole c     | Rifampin d            |
| Lopinavir c        | Rifamycin d           |
| Mibefradil c       | Rifapentin d          |
| Miconazole c       | St. John's Wort d     |
| Mifepristone                  | Troglitazone                     |
| Nefazodone c       |                                  |
| Nelfinavir c       |                                  |
| Norfloxacin                   |                                  |
| Norfluoxetine                 |                                  |
| Posaconazole c     |                                  |
| Ritonavir c        |                                  |
| Saquinavir c       |                                  |
| Starfruit                     |                                  |
| Telaprevir c       |                                  |
| Telithromycin c    |                                  |
| Tipranavir c       |                                  |
| Troleandomycin c   |                                  |
| Verapamil a        |                                  |
| Voriconazole c     |                                  |

- A moderate inhibitor is one that causes a > 2-fold increase in the plasma AUC values or 50-80% decrease in clearance.
- A weak inhibitor is one that causes a > 1.25-fold but < 2-fold increase in the plasma AUC values or 20-50% decrease in clearance.
- A strong inhibitor is one that causes a > 5-fold increase in the plasma AUC values or more than 80% decrease in clearance, and are NOT allowed during this clinical trial.
- Strong inducers are not allowed during this clinical trial.

Source: Prescribing Information for Regorafenib (SEP 2012) and Indiana University School of Medicine, Division of Clinical Pharmacology (Update: 25 JAN 2012):  
<http://medicine.iupui.edu/clinpharm/ddis/table.aspx>

